5.1.2　Secondary endpoint(s)

5.1.2.1　Significant secondary endpoint

Improvement from baseline (prior to administration) in symptoms (pain) associated with the target lesion after 3 months of sclerotherapy*.

*: For pain rating scales, VAS is used for patients aged 6 years and older. Face scale is used for patients aged 2 to 5 years of age, however, evaluation for this group is not mandatory. For guardians, VAS is used if the patient is 6 to 14 years old, and Face scale is used if the patient is 5 years old or younger, and the evaluation should be done from the guardian’s perspective.. (The evaluation scale is shown in Appendix 2.)

For patients

| Patient Age | | 0 year old | 1 year old | 2-4 years old | 5 years old | 6-7 years old | 8-12 years old | 13-14 years old | 15 years and older |
| --- | --- | --- | --- | --- | --- | --- | --- | --- | --- |
| Pain | VAS |  |  |  |  | X | X | X | X |
|  | Face scale |  |  | X** | X** |  |  |  |  |

**: Evaluation is not mandatory.

For guardians

| Patient Age | | 0 year old | 1 year old | 2-4 years old | 5 years old | 6-7 years old | 8-12 years old | 13-14 years old | 15 years and older |
| --- | --- | --- | --- | --- | --- | --- | --- | --- | --- |
| Pain | VAS |  |  |  |  | X | X | X |  |
|  | Face scale | X | X | X | X |  |  |  |  |

[Basis for setting up].

In diffuse lesions, we considered it particularly important to see improvement in pain, therefore we set this as a significant secondary endpoint.

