5.1.2.2　Other secondary endpoints

The efficacy endpoints are as follows:

1) Reduction rate in volume of venous malformations at the time of 3 months after intervention

2) Improvement in symptoms such as pain originated from venous malformations at the time of 1 month (4 weeks) after intervention^＊^

3) Improvement of QOL (ADL) at the time of 3 months after intervention^＊＊^

*: For pain rating scales, VAS is used for patients aged 6 years and older; Face scale is used for patients aged 2 to 5 years, however, evaluation for this group is not mandatory. For guardians, VAS is used if the patient is 6 to 14 years old, and Face scale is used if the patient is 5 years old or younger to evaluate from the guardian’s perspective. (The evaluation scale is shown in Appendix 2.)

**: For the QOL evaluation scales, the EQ-5D Japanese version is used for patients aged 15 years and older, and the PedsQL Japanese version for patients aged 5 to 14 years, however, evaluation for children aged 5 years is not mandatory. For guardians, the PedsQL Japanese version (proxy evaluation) is used if the patient is 14 years old or younger, and the evaluation should be done from the guardian’s perspective. The selection of the QOL evaluation scale was determined based on the review of the QOL Evaluation Method Review Committee. (The evaluation scale is shown in Appendix 2.)

For patients

| Patient Age | | 0 year old | 1 year old | 2-4 years old | 5 years old | 6-7 years old | 8-12 years old | 13-14 years old | 15 years and older |
| --- | --- | --- | --- | --- | --- | --- | --- | --- | --- |
| Pain | VAS |  |  |  |  | X | X | X | X |
|  | Face scale |  |  | X***. | X***. |  |  |  |  |
| QOL | EQ-5D |  |  |  |  |  |  |  | X |
|  | PedsQL |  |  |  | X***. | X | X | X |  |

****: Evaluation is not mandatory.

For guardians

| Patient Age | | 0 year old | 1 year old | 2-4 years old | 5 years old | 6-7 years old | 8-12 years old | 13-14 years old | 15 years and older |
| --- | --- | --- | --- | --- | --- | --- | --- | --- | --- |
| Pain | VAS |  |  |  |  | X | X | X |  |
|  | Face scale | X | X | X | X |  |  |  |  |
| QOL | PedsQL | X | X | X | X | X | X | X |  |

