8.2.2.2　Analysis for secondary endpoints

8.2.2.2.1　Analysis for important secondary endpoints

For the symptom (pain) score associated with the target lesion at 3 months after sclerotherapy, the median -1-fold change from baseline (prior to administration) and its 95% confidence interval will be estimated. Also, a Wilcoxon signed-rank test is performed under a null hypothesis of "the median -1-fold change from baseline to 3 months after intervention in the population is less than or equal to 0." The significance level is set at 2.5% one-sided.

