8.2.2.2.2　Analysis for other secondary endpoints

(1) The median percent reduction from baseline (prior to administration) and its 95% confidence interval for the reduction rate (volume) of the target lesion at 3 months after sclerotherapy will be estimated. Also, a Wilcoxon signed-rank test is performed under a null hypothesis of "The median reduction rate (volume) of the target lesion at 3 months after sclerotherapy is less than or equal to zero. The significance level is set at 2.5% one-sided.

(2) The median -1-fold change from baseline (prior to administration) to 1 month post sclerotherapy and its 95% confidence interval for the symptom (pain) score associated with the target lesion at 1 month (4 weeks) post sclerotherapy will be estimated. Also, a Wilcoxon signed-rank test is performed under a null hypothesis of "the median -1-fold change from baseline to one month after sclerotherapy in the population is less than or equal to zero." The significance level is set at 2.5% one-sided.

(3) The median change from baseline (prior to administration) to 3 months after sclerotherapy and its 95% confidence interval for the QOL score will be estimated. A Wilcoxon signed-rank test is performed under a null hypothesis of "the median change from baseline to 3 months after sclerotherapy for the population is less than or equal to zero." The significance level is set at 2.5% one-sided.

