8.6.2.1 　Diffuse lesions

Patients with diffuse lesions are considered to be more prevalent than those with cystic lesions, however, considering the feasibility of the study, taking into account the variation in the number of patients depending on year, we considered it appropriate to have about the same number of patients as the target number of patients with cystic lesions, which is 22 cases including dropouts (under 15 years old: target 10 cases).

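### The QOL analysis sets one median and one signed-rank test per cohort for a score that comes from EQ-5D in patients aged 15 and over and from PedsQL in younger ones

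*Protocol*

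**What the plan says.** Section 8.2.2.2.2(3) treats QOL as one variable. The median change from baseline to 3 months and "its 95% confidence interval for the QOL score will be estimated", and the null hypothesis tested is that "the median change from baseline to 3 months after sclerotherapy for the population is less than or equal to zero". The level is fixed too: "The significance level is set at 2.5% one-sided". The Summary of Protocol repeats this under the main statistical methods. The opening of section 8 separates cystic from diffuse lesions. That is the only split of the main analysis.

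Section 5.1.2.2 assigns the instrument by age: "the EQ-5D Japanese version is used for patients aged 15 years and older, and the PedsQL Japanese version" for ages 5 to 14, with self-report optional at age 5. Guardians of patients aged 14 or younger also complete a proxy PedsQL. No conversion between instruments, stratification by instrument or choice of rater is stated.

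Section 8.6.2.1 sets the age mix for the diffuse cohort ("under 15 years old: target 10 cases" out of 22) and gives the same target for the cystic cohort.

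Pain is handled in parallel. Section 8.2.2.2.1 opens "For the symptom (pain) score associated with the target lesion at 3 months after sclerotherapy" and fixes one median and one test. Section 5.1.2.1 says that "VAS is used for patients aged 6 years and older. Face scale is used for patients aged 2 to 5", and adds guardian ratings up to age 14.

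**The concern.** The signed-rank test orders absolute changes across all subjects and sums the ranks of the positive ones. That is meaningful only if a change of a given size means the same in every subject. EQ-5D and PedsQL are different questionnaires with different scoring. Pooled, the instrument with numerically larger changes takes the high ranks whatever the clinical size of those changes, and the median falls at a point on a mixed list that belongs to neither scale.

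Three things are at stake: whether the reported QOL median can be read at all, whether the p-value describes the cohort or mainly one age group, and how much power is lost. Because recruitment aims for both age groups in each cohort, mixing is planned and does not depend on an unusual sample.

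**Working it through.** **Inputs.** From the Protocol: 22 subjects per cohort (8.6.1), of whom 10 are under 15 (8.6.2.1), leaving 22 − 10 = 12 aged 15 or over; one-sided 2.5% (8.2.2.2.2). Assumed: PedsQL changes have an SD between 1 and 80 times that of EQ-5D changes; all 22 subjects give one score each; changes are normal. Appendix 2, which holds the scales, is not shown, so the ratio cannot be fixed.

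**The plan's own figure.** The Protocol gives no figure for QOL. Its sample size of 19 for the primary endpoint (20% against 50%, one-sided 2.5%, 80% power) reproduces: with 19 subjects and success at 8 or more responders, exact alpha is 0.0233 and power 0.820.

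**Rank weight.** The total rank sum is 22 × 23 / 2 = 253. If every PedsQL change is larger in absolute size than every EQ-5D change, the 12 older subjects hold ranks 1–12, sum 12 × 13 / 2 = 78, and the 10 children hold 253 − 78 = 175. Their share is 175 / 253 = 69%, against 10 / 22 = 45% of subjects. With 7 or 5 children the limit is 53% or 40%, against 32% or 23% of subjects.

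**Test.** The exact critical value for n = 22 is W+ ≥ 188 (tail 0.0231). In the limiting case:
- All children improve: 188 − 175 = 13 of the older subjects' 78 rank points are enough for significance.
- All 12 older subjects improve and children's signs are random: expected W+ = 78 + 175 / 2 = 165.5, below 188.
- All 12 improve and all 10 children worsen: W+ = 78, p = 0.94. The reverse: W+ = 175, p = 0.060, although 12 of 22 worsened.

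The median and the test can also point in opposite directions. Take EQ-5D changes of 0.01 to 0.12 and PedsQL changes of −3 to −12. The 11th and 12th ordered values are 0.01 and 0.02, so the pooled median is +0.015 while p = 0.94.

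**Power by SD ratio** (simulation, 12 EQ-5D and 10 PedsQL subjects, effect 0.8 SD; repeat simulations agree to about one percentage point):

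| SD ratio | Children's rank share | Power, effect in adults only | Power, effect in both | Rejection under no effect |
|---|---|---|---|---|
| 1 | 45% | 40% | 93% | 0.022 |
| 2 | 55% | 28% | 92% | 0.024 |
| 5 | 63% | 19% | 88% | 0.023 |
| 10 | 66% | 16% | 85% | 0.024 |
| 80 | 69% | 14% | 83% | 0.023 |

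The test in the 12 adults alone has 67% power. Ranking within instrument and summing the two statistics gives about 39% (adults only) and 92% (both) at every ratio.

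**Pain.** The Face scale applies only at age 5 or younger, and no number of such patients is planned. If 3 of 22 used it and VAS were the wider scale, their rank weight would be 14% at equal spread, 9% at ratio 2 and 4% at ratio 10, against 14% of subjects. VAS would then simply decide the test.

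**The case against.** **Pooling is inferred from a singular noun, and the analysis plan can define the score.** Section 8.2.1 does send all analyses to a statistical analysis plan, which may name the instrument and rater. But the Protocol is not silent here: it fixes one score, one median, one interval and one test per cohort. A plan with instrument-specific analyses would replace that wording rather than complete it.

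**The age subgroups already separate the instruments.** This stands in part. Section 8.2.2.4 cuts at age 15, the boundary between EQ-5D and PedsQL, so an EQ-5D-only result is already planned. Those analyses add to the main one without replacing it, and they spread PedsQL over three subgroups, so no planned result covers all PedsQL subjects.

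**The loss of power is a worst case.** This stands. A reader might compare 13–14% pooled with 67% in adults alone and blame the instruments for the whole gap. On equal scales pooled power is already only about 40%, because that scenario assumes no benefit in children. With benefit in both groups the pooled test keeps 83% even at ratio 80. The documents do not suggest that benefit is confined to one age group.

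**A reader might infer that pain has the same fault, and that the subgroup of age 5 and younger shows that Face-scale data enter the pain score.** The documents do not support this. That subgroup also serves the primary endpoint and the volume reduction rate. Section 3.2.2.3 makes pain and QOL collection optional at age 5 or younger, and those children need prior committee review to enter.

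**Conclusion.** The point holds for QOL at moderate severity. The Protocol specifies a pooled analysis that does not fit its own instruments: the median has no unit, and subjects' weights depend on scoring width. The missing unit follows from the text alone. The weighting and power figures rest on the assumed SD ratio, on PedsQL being the wider scale, and on 12 and 10 subjects. If EQ-5D were the wider scale, the dominance would reverse and the fault would remain.

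The evidence does not support inflated type I error: with no effect in either group and symmetric changes, the test keeps its level. Nor does it support treating this as critical to the trial, since QOL is the last of three other secondary endpoints and neither the primary endpoint nor the sample size is affected. For pain, only a minor clarification of scale and rater follows.

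**What to change.** In section 8.2.2.2.2(3) and the matching item of the Summary of Protocol, estimate the median change and 95% confidence interval separately for EQ-5D and PedsQL within each cohort, and give no pooled median. Make self-report the main PedsQL analysis and report guardian proxy ratings separately. If one QOL test per cohort is wanted, rank within instrument and sum the two signed-rank statistics; its null distribution is exact and it does not depend on the scale ratio.

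For pain, add one sentence to 8.2.2.2.1 and 8.2.2.2.2(2): Face-scale changes and guardian ratings are not merged with patient VAS changes in one median or test.

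The cost is wording only; no visit, questionnaire or sample size changes. The downside is fewer subjects per estimate: about 12 for EQ-5D and at most about 10 for PedsQL, fewer still on self-report, because children under 5 have only a proxy rating and self-report is optional at age 5. The choice of instrument and rater should be fixed before the data are, so that it cannot follow the results.

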8.2.2.3　Analysis for other endpoints

The percentage of each category (significant improvement, moderate improvement, unchanged, and exacerbation) for the change in appearance at 3 months after sclerotherapy will be estimated. We will also estimate the percentage of significant improvement or moderate improvement and its 95% confidence interval, under a null hypothesis of "the percentage of cases with significant improvement or moderate improvement is less than 20%." and then perform a test based on the binomial distribution. The significance level is set at 2.5% one-sided.

8.2.2.4　Subgroup analysis

For "8.2.2.1 Analysis for primary endpoint" and "8.2.2.2 Analysis for secondary endpoints," a subpopulation analysis will be conducted for four age categories: 5 years and younger, 6 to 11 years, 12 to 14 years, and 15 years and older.

8.2.3　Safety analysis

(1) For each adverse event and adverse drug reaction, the number of subjects and incidence rate are shown. The number of subjects and the incidence rate is tabulated by organ, symptoms findings, and grade of adverse event. For serious adverse events, the number of subjects and the rate of occurrence should is indicated and listed.

(2) Summary statistics of laboratory measurements are tabulated by survey period.

8.3　Handling of missing values

No inputation will be performed in case of missing data.

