8.1　Analysis population

8.1.1　Definition of analysis population

The population to be analyzed is defined as follows.

(1) Full analysis set (FAS): all subjects who were administered the study drug

(2) Per protocol set (PPS): The subjects in the FAS, excluding those with the following serious violations of the study protocol regulations in terms of study methods, concomitant therapy, etc. The PPS will be set for the purpose of confirming the stability of the primary analysis for the efficacy endpoints.

・Inclusion criteria violation

・Exclusion criteria violation

・Significant deviations from the study protocol that could affect the evaluation of efficacy

(3) Safety analysis set (SAS): Same as FAS

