8.2.2　Efficacy analysis

8.2.2.1　Analysis for primary endpoint

For the number of subjects who achieve more than 20% reduction from baseline (prior to administration) in the volume of venous malformations at 3 months of treatment with the study drug, if the null hypothesis is "the proportion of the population achieving more than 20% reduction from baseline in the volume of venous malformations at 3 months of treatment with the study drug is less than 20%", a test based on the binomial distribution is performed. The significance level is set as 2.5% one-sided. The 95% confidence interval between the proportion of subjects achieving more than 20% reduction from baseline in the volume of venous malformations at 3 months of treatment with the study drug and the proportion based on the score test will also be estimated.

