8.6.2　Basis for setting

8.6.2.1 　Cystic lesions

For the difficult-to-resect venous malformations (cystic lesions) that are the subject of this trial, no improvement is expected as a natural history. However, we set the threshold for this study at 20% because we believe that the percentage of subjects who achieve CR (target lesion disappearance) and PR (target lesion volume reduction of at least 20%), which were defined as the achievement criteria, must improve by at least 20% when the treatment is administered.

Studies evaluating MRI-based monoethanolamine oleate for difficult-to-resect venous malformations are limited. Kaji et al.^10)^ reported a study of lesion reduction rates using MRI in subjects with venous malformations. From the box-and-whisker diagram shown for venous malformations (60 cases), it can be read that the median is approximately 25%. Since the median value corresponds to the 50th percentile of the distribution, the percentage of subjects with a reduction rate of 20% or greater would be expected to be greater than 50% as read from the figure. The study by Alexander et al.^13)^ of the reduction rate using MRI for venous malformations also suggests that the proportion of subjects with a reduction rate of 20% or greater would be expected to be 50% or greater. Kaji et al. converted lesion reduction rate from area (Alexander et al. converted from volume), which is not the same as the evaluation of target lesion volume set for this trial, but we considered the reduction rates in these studies to be appropriate for this trial and expected the proportion of CR and PR to be 50% or more.

In this setting, the number of cases needed to obtain 80% power in a test based on a binomial distribution with a significance level of 2.5% one-sided is 19. Considering dropout cases, the target number of cystic lesion patients was set at 22 cases. In order to ensure a certain number of cases in the younger age group in actual clinical practice, the target number of cases was set for each age group as follows
 (under 15 years old: target 10 cases).

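### The no-imputation rule takes treated subjects without a 3-month MRI out of the primary responder denominator, and at three losses this can turn a failed test into a success

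*Protocol*

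**What the plan says.** Section 8.1.1 defines the primary efficacy population: "Full analysis set (FAS): all subjects who were administered the study drug". Section 8.1.2 confirms that the FAS is primary for efficacy, separately for cystic and diffuse lesions.

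For the responder endpoint (at least 20% volume reduction at 3 months), section 8.2.2.1 specifies that "a test based on the binomial distribution is performed" against a null proportion of 20%. It adds: "The significance level is set as 2.5% one-sided". It does not write out the denominator.

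Section 8.3 is one sentence covering every endpoint: "No inputation will be performed in case of missing data". No section says how a treated subject without a 3-month volume counts in the responder proportion.

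Section 8.6.2.1 (cystic lesions) gives 19 as "the number of cases needed to obtain 80% power in a test based on a binomial distribution" at one-sided 2.5%, having "expected the proportion of CR and PR to be 50% or more". It continues: "Considering dropout cases, the target number of cystic lesion patients was set at 22 cases". No dropout rate is given. The diffuse cohort is also set at 22 including dropouts, on feasibility grounds and without a power statement.

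**The concern.** A treated subject with no evaluable 3-month MRI has no volume change. Entering that subject as not having achieved the reduction assigns a value to a missing outcome, which section 8.3 appears to forbid. The step from 19 to 22 points the same way, because it treats dropouts as leaving the analysed number. Together these make the primary test a complete-case test on fewer subjects than the FAS that the protocol names as primary.

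The trial has one arm and compares a proportion with a fixed threshold, so no control group shares the missingness. If those who do not return are non-responders, removing them raises the estimated proportion directly. Several discontinuation reasons in section 7.1 (withdrawal of consent, adverse events, surgery, hospital transfer) could be related to outcome. At stake is whether a cohort's primary conclusion can depend on who came back for imaging.

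**Working it through.** **Inputs.** Null rate 20% and expected rate 50% (section 8.6.2.1); exact binomial test, one-sided 2.5% (section 8.2.2.1); 19 needed and 22 treated (section 8.6.2.1). The allowance is therefore 22 − 19 = 3 subjects, or 3/22 = 13.6%.

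**Formulas.** For n analysed subjects, the critical value c is the smallest r with P(X ≥ r | n, 0.20) ≤ 0.025. The actual type I error is P(X ≥ c | n, 0.20), and the power is P(X ≥ c | n, 0.50).

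**Reproducing the protocol's figure.** At n = 18, c = 8 and power is 76.0%. At n = 19, c = 8, type I error is 0.0233 and power is 82.0%. Nineteen is the smallest n that reaches 80%, so the stated figure is right.

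**Dropping missing subjects, over the protocol's own range of 0 to 3 losses:**

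| Lost of 22 | Analysed n | Critical value | Actual type I error | One-sided p for 8 responders | Result with 8 | Power at 50% |
|---|---|---|---|---|---|---|
| 0 | 22 | 9 | 0.0201 | 0.0561 | fails | 85.7% |
| 1 | 21 | 9 | 0.0144 | 0.0431 | fails | 80.8% |
| 2 | 20 | 9 | 0.0100 | 0.0321 | fails | 74.8% |
| 3 | 19 | 8 | 0.0233 | 0.0233 | succeeds | 82.0% |

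**Where the decision changes.** If all 22 stay in the denominator, 9 responders are needed whatever the number missing. If missing subjects are dropped, 9 are still needed at n = 21 and n = 20, so the decision is the same. Only at n = 19 does the requirement fall to 8. There, 8 responders succeed as 8/19 (42.1%) and fail as 8/22 (36.4%). Seven responders fail either way (7/19 gives p = 0.0676), and nine succeed either way.

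**Worst case for type I error.** Let the true rate among 22 treated subjects be 20%, and suppose three non-responders are always lost. Success then needs 8 or more responders among the 22:

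- P(X ≥ 8 | 22, 0.20) = 0.0561
- with all 22 counted, P(X ≥ 9 | 22, 0.20) = 0.0201

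If only one or two non-responders are lost, 9 responders are still required and the chance stays at 0.0201. If three are lost at random, the type I error is that of n = 19, 0.0233, which is within 2.5%.

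**Power with missing subjects counted as non-responders.** The critical value is 9/22 and the assumed rate is 50% among observed subjects, so power is P(X ≥ 9 | 22 − m, 0.50) with m missing:

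- m = 0: 85.7%
- m = 1: 80.8%
- m = 2: 74.8%
- m = 3: 67.6%

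**The case against.** The exclusion is inferred, because no section writes out the denominator. Section 8.1.2 names the FAS as primary, section 8.1.3 sends individual cases to a review meeting before the data are fixed, and section 8.2.1 refers to a SAP that is not shown and could define how non-evaluable subjects count. One could also argue that counting them as not having achieved the reduction is an endpoint definition and not imputation. This stands in part: the protocol does not say in words that such subjects are dropped. But section 8.3 has no exception, and a non-responder rule in the SAP would sit uneasily with it. Settling the matter case by case, late in an open-label trial, is weaker than a rule fixed in advance.

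The exposure is also limited. Treatment is a single session, with one optional repeat for diffuse lesions. The 3-month MRI is scheduled for discontinued subjects too (sections 6.2.4.2 and 6.2.4.3), with a window of ±14 days. Within the allowance, the decision changes only with exactly three missing and exactly 8 responders. All of this stands and lowers the severity, but scheduling an MRI does not say how a missing one is handled.

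Two stronger readings are tempting, and the document supports neither. A reader might infer that the 80% power is misstated because power is 74.8% at n = 20. The protocol claims 80% only for 19, only for the cystic cohort, and correctly. It does not claim 80% for every number from 19 upward. The dip comes from the discreteness of the exact test, and a non-responder rule does not remove it. A reader might also infer that the type I error is inflated in general. It is not: the 5.6% needs three losses, all of them non-responders, and the protocol gives no evidence that loss will follow non-response.

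**Conclusion.** The point holds as a should-fix. As written, the no-imputation rule and the dropout allowance make the primary responder test, on their natural reading, a complete-case test in both cohorts, although the FAS is named as primary. At three losses the same 8 responders among 22 treated subjects pass or fail according to the denominator (p = 0.0233 against p = 0.0561). The worst-case chance of success at a true 20% rate is 5.6% instead of 2.0%. With one or two losses the decision is unchanged, and only the estimated proportion is raised.

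This rests on 22 treated subjects per cohort, the exact binomial test and no more than three missing. The 5.6% further assumes that all three missing subjects are non-responders.

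**What to change.** In sections 8.3 and 8.2.2.1, state that for the primary responder endpoint in each cohort the denominator is all FAS subjects. A subject without an evaluable 3-month MRI (3 months after the additional administration, where one was given) counts as not achieving the 20% reduction. Word section 8.3 so that this rule is an explicit exception to the no-imputation sentence. Keep the evaluable-only analysis as a sensitivity analysis.

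As a consequence for the cystic cohort only, note in section 8.6.2.1 that with 22 treated and a critical value of 9/22, power at a 50% rate is 85.7%, 80.8%, 74.8% and 67.6% with 0, 1, 2 and 3 missing. The figure of 19 for 80% power can stay as the minimum number of evaluable subjects.

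The change is to wording only and adds no visits or subjects. The downside is less favourable power if subjects are lost: at three missing, 67.6% instead of the 82.0% of the evaluable-only test. Because discontinued subjects are already scheduled for the 3-month MRI, few should be missing.
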